## Abstract

**Background:**

Up to 80% of women use some form of pharmacological analgesia during labour and birth. The side effects of pharmacological agents are often incompatible with the concurrent use of non-pharmacological pain relieving strategies, such as water immersion, ambulation and upright positioning, or may have negative effects on both the mother and fetus. Sterile water injections given into the skin of the lumbar region have been demonstrated to reduce back pain during labour. However, the injections given for back pain have no effect on abdominal contraction pain. The analgesic efficacy of sterile water injections for abdominal pain during childbirth is unknown. The injections cause an immediate, brief but significant pain that deters some women from using the procedure. This study aims to investigate the use of water injections given intradermally into the abdomen to relieve labour contraction pain. A vapocoolant spray will be applied to the skin immediately prior to the injections to reduce the injection pain.

**Methods:**

In this pragmatic, placebo controlled trial 154 low-risk women in labour at term with a labour pain score ≥ 60 on a 100 millimitre visual analogue scale (VAS) will be randomly allocated to receive either six injections of sterile water or a sodium chloride 0.9% solution as a placebo (0.1–.0.3 ml per injection). Three injections are given along the midline from the fundus to the supra-pubis and three laterally across the supra-pubis. The primary outcome will be the difference in VAS score 30 min post injection between groups. Secondary outcomes include VAS score of the injection pain on administration, VAS score of labour pain at 60 and 90 min, maternal and neonatal birth outcomes.

**Discussion:**

Access to effective pain relief during labour is fundamental to respectful and safe maternity care. Pharmacological analgesics should support rather than limit other non-pharmacological strategies. Sterile water injections have the potential to provide an alternative form of labour pain relief that is easy to administer in any labour and birth setting, and compatible with other non-pharmacological choices.

**Trial registration:**

ANZCTR (ACTRN12621001036808) Date submitted: 22/06/2021. Date registered: 05/08/2021. https://www.anzctr.org.au/

**Supplementary Information:**

The online version contains supplementary material available at 10.1186/s13063-022-06093-3.

## Background

In countries such as Australia and the United Kingdom up to 80% of laboring women use some form of pharmacological analgesia [1, 2]. Current options for pharmacological analgesia in labour have changed little in past decades with the most common choices being opioids, nitrous oxide inhalation and neuraxial (epidural) analgesia. The analgesic effectiveness of opioids such as morphine and pethidine is minimal with most women continuing to report moderate to severe pain [3]. Opioids are more likely to provide drowsiness than analgesia which has highlighted the ethical problem of primarily providing sedation in response to a woman’s request for pain relief [4]. Opioids readily cross the placenta and are found in breast milk.. The metabolism of pethidine results in the formation of norpethidine, which is associated with neuronal depression in the neonate up to 60 h post-birth and feeding difficulties for up to 6 weeks post partum [5, 6].

The analgesic effectiveness of nitrous oxide varies from no difference to the placebo to similar to that opioids [7]. Whilst generally considered safe recent studies have highlighted metabolic, oxidative, genotoxic, and transgenerational epigenetic effects from prolonged exposure. A 1 to 3 h exposure to 50% nitrous oxide (a common dose during labour) inactivates methionine synthase in the mother and fetus which can take 3 to 5 days to recover. This increases the potential for haematological disorders such hypercoagulation, particularly in Vitamin B12 deficient women [8].

In high income countries epidurals are used by up to 70% of labouring women [1, 9]. Epidurals have been shown to provide more effective analgesia than opioids [10]. Whilst generally considered safe epidurals can have immediate, medium and possibly long term side effects. Epidurals are strongly associated with maternal fever during labour resulting in increased use of antibiotics [11], prolonged labour and assisted birth (vacuum extraction or forceps) [12].

Many women will use a combination of pharmacological and non-pharmacological strategies to achieve personal and psychological control over the pain they are experiencing, rather than seeking a total elimination of pain [13]. All of the current pharmacological agents are largely incompatible with non-pharmacological options, particularly those involving ambulation, upright positions or water immersion [14]. Both nitrous oxide and opioids can result in sedation and impaired balance that may increase the risk of falls injuries. Epidurals require intravenous cannulation, fluid administration, urinary catheterisation and continuous fetal monitoring. These restrict mobility and reduce a woman’s ability to adopt favourable positions for labour and birth.

A recent placebo controlled trial demonstrated the efficacy of sterile water injections into the lumbar region to relieve back pain in labour with no detrimental side effects [15]. Back pain in labour is different to and may occur independently from abdominal labour pain [16]. Furthermore, the injections given into the lumbar region for back pain have no effect on abdominal contraction pain [15, 17]. Injections of sterile water are acutely painful for a brief period and this is known to act as a deterrent to both women and clinicians [18, 19]. Theoretically, the acute pain associated with the injection (noxious stimulus), tissue distension and increased osmotic pressure stimulate gate control of pain and endorphin release to reduce pain [20, 21]. A moderate reduction in injection pain, through the administration of one rather than four injections, still results in significant analgesia though for a shorter duration [17]. Though no reliable method to achieve this is currently in use [17]. A non-placebo exploratory trial and case study suggests the potential for using water injections to relieve abdominal labour pain [22, 23].

Vapocoolant sprays consist of rapidly evaporating solvents that quickly reduce skin temperature to produce a numbing effect and result in a moderate reduction in pain scores [24]. The only reported side effects are the cold sensation and occasionally mild transient erythema at the treated sites [24].

## Objectives

We aim to test the effectiveness of sterile water injections given into the abdomen to relieve labour contraction pain. We will also apply a vapocoolant spray immediately prior to the injections to reduce the injection discomfort.

## Methods: participants, interventions and outcomes

### Trial design

This will be a pragmatic randomised placebo-controlled superiority trial specifically designed to provide evidence of the efficacy of water injections to relieve abdominal labour pain. Following provision of informed consent participants will be randomised to receive either water injections (intervention) or normal saline injections (control). For both groups pre-injection preparation with a vapocoolant spray will occur. The participant flow is demonstrated in Fig. 1.

**Fig. 1 Fig1:**
[figure not shown]
Participant flow

### Study setting

The trial will be conducted at a tertiary maternity unit in Brisbane Australia providing labour and birth care for approximately 5000 women annually. The research site provides both birth-centre and standard labour and birth care.

### Study population and recruitment

We plan to recruit and consent provisionally eligible women in the late antenatal period (36–37 weeks). Whilst this may include women who are either ineligible at the onset of labour, or remain eligible but decline participation, this strategy will reduce the need to rely on clinical staff, in the birth suite and birth centre, to identify, screen, provide participant information and complete consent documentation whilst also providing care. This also minimises the ethical issue of recruiting and consenting in labour when pain and/or effect of medications may impact on the woman’s capacity to consent to participation in research. Women may also be recruited upon presentation to the Birth Centre or Birth Suite in early labour.

The study site offers a number of models providing care to women likely to meet the inclusion criteria. These are broadly defined as Midwifery and General Practitioner (GP) Shared Care. Midwifery care models are provided by the Birth Centre, Midwifery Group Practices (MGP). Women attending GP shared care all return at 36 weeks gestation, providing an opportunity to discuss the trial and participation. Women attending Birth Centre and MGP antenatal clinics will be approached during their 36–37 week visit. Consent processes will be undertaken by the Research Midwives or in their absence, a midwife who is not providing direct care to the woman.

In the event that COVID-19 restrictions prevent a face to face consent process Potential participants will be provisionally approached during the routine antenatal video conference and asked if they are interested in discussing participation in the trial with a research midwife. Interested participants will be asked for contact details (email address, mobile phone number) to arrange a suitable time for a discussion regarding the trial and potential participation using their preferred video conferencing format (e.g. FaceTime, Zoom, Teams). A link to the SATURN Trial Participant Information and e-Consent form will be sent to the potential participant so they can review the trial information and consider any questions prior to the discussion.

The e-Consent form requires a three step verification process consisting of i) indicating ‘yes’ to verify statements that appear on the consent form; ii) drawing a signature on the screen either with a mouse or device touch screen; iii) final declaration that the participant is aware that submitting the form with the signature is equivalent to providing a signed consent form. The participants are then able to download a copy of the completed and signed SATURN trial Participant Information and e-Consent form and a pdf copy is sent to a designated email address.

This trial does not involve the collection of biological specimens.

### Eligibility criteria

Eligibility criteria consists of ≥16 years of age, singleton cephalic (head down) pregnancy, ≥ 37 weeks gestation, spontaneous or induced labour, no serious concurrent medical conditions (pre-eclampsia, coagulopathy, diabetes other than diet controlled), cognitively capable of providing consent, able to read and understand instructions written in English. Upon admission to the birth suite randomisation will occur when the participant’s self-assessment of labour pain ≥60 mm (Visual Analogue Scale [VAS] 0-100 mm, 0 = no pain 100 = worst conceivable pain), and requesting pain relief.

### Randomisation and blinding

Randomisation schedules will be prepared by a statistician independent of the study using computer-generated pseudo-random numbers, using varying block sizes. Identical ampoules of either normal saline or sterile water will be pre-prepared by the study site pharmacy and packed in opaque black plastic packets and arranged based on the allocation schedule. Following confirmation of consent two midwives will remove the next ampoule in sequence and administer the injections. Normal saline for injection 0.9% will be used as the placebo solution. Normal saline is an active placebo resulting in some minor injection discomfort and some degree of analgesia, it has been used successfully in previous placebo controlled trials [15, 25]. Outcome assessment will be undertaking by the midwife administering the injections. The use of the vapocoolant in both the intervention and control arms will reduce the chance of participant and outcome assessor unbinding as all women will experience cooling effect of the vapocoolant. The data analysis will be blinded to the allocated group.

### Interventions

Participants in the intervention groups will receive intradermal injections of 0.1–0.3 ml of sterile water into six anatomical points on the abdomen (Fig. 2). The volume required to be injected is based on the visual estimation of the resulting blister or ‘bleb’. If the needle is inserted beyond the intradermal layer the bleb does not occur and the needle may require repositioning to achieve the correct anatomical depth. The location of the injections is based on a previous RCT of water injections versus acupuncture and early studies that used intradermal injections of local anaesthetic into the abdomen to relieve pain in labour [22, 26, 27]. These studies suggested that injections given in a line extending medially from the fundus to the suprapubic area and extending laterally from the suprapubic region will produce an effective analgesic response. As the experience and location of contraction pain varies considerably the precise location and number of injections may vary based on the areas of greatest discomfort indicated by the woman. Otherwise there will be no special criteria for modifying the allocated interventions. The injection procedure will be ceased at the request of the participant. Up to three repeat courses of injections will be provided for women who request them.

**Fig. 2 Fig2:**
[figure not shown]
Injection sites

Data items such as location of injections, VAS and duration of effect will be collected for the initial and repeat injections. To improve adherence to study protocols all midwives administering water injections will be credentialed in this technique using a competency based assessment that was used successfully in our previous trials [22, 28]. Midwives will indicate the number and location of the injections given on the data collection form which will be monitored by the research officers for adherence to the protocol.

Participants in the control group will receive intradermal injections of 0.1–0.3 ml of normal saline 0.9% for injection into the abdomen as previously described. All other components of the administration will be the same as the intervention group.

Both groups will also receive skin preparation immediately prior to the injections using the vapocoolant spray PainEase® manufactured by Gebauer. PainEase® spray contains 1,1,1,3,3-Pentafluoropropane and 1,1,1,2-Tetrafluoroethane which are non-flammable and unlike ethyl chloride are not absorbed through the skin and therefore safe to use in pregnancy. The cooling effect occurs through the rapid evaporation. PainEase is registered with the Australian Therapeutic Goods Administration as a vapocoolant topical anaesthetic available to the general public. The injection points will be sprayed with PainEase® spray at a distance of 12 cms from skin for a period of 5 to 8 s immediately prior to administering the injections*.*

Implementing the injections of sterile water of saline will not require alteration to usual care pathways. Participants in both arms will have access to any form of standard care including combinations of currently available pharmacological and non-pharmacological options.

Provisions for post-trial care There is no anticipated harm and compensation for trial participation. In the event that participants experience harm as a result of participation they will be able to apply for compensation through trial insurance provided by the sponsor.

### Outcomes

The primary outcome for the trial is the mean difference in VAS scores of labour pain between intervention and control groups at 30 min following the administration of the injections. Secondary outcomes include the number of women experiencing an at least 30% or 50% reduction in pain following the injections. This is the measure of analgesic effectiveness recommended in the Cochrane Review of water injections for back pain in labour [29]. Other secondary outcomes are detailed in Table 1.

**Table 1 Tab1:** Schedule of enrolment, interventions and assessments

		Study period					
			Post-allocation				Close-out
	Enrolment	Allocation	*Time periods after injection*			*1–14 days post birth*	*From perinatal database*
TIMEPOINT**			*30 min*	*60 min*	*90 min*		
**ENROLMENT:**							
**Eligibility screening**	X	X					
**Signed consent form**	X						
**Randomisation**		X					
**INTERVENTIONS:**							
***Sterile water injection***		X					
***Normal Saline placebo injection***		X					
***Vapocoolant spray***		X					
**ASSESSMENTS:**							
***Cervical dilation***		X					
***VAS of labour pain prior to injections***		X					
***VAS of injection pain***		X					
***VAS of labour pain post injection***			X	X	X		
***At least 30% reduction in VAS of pain***			X				
***At least 50% reduction in VAS of pain***			X				
***Pharmacological analgesia use***		X					X
***Non-pharmacological analgesia use***		X					X
***Duration of labour***							X
***Augmentation of labour***							X
***Mode of birth***							X
***Estimated blood loss at birth***							X
***Apgar scores***							X
***Type of neonatal resuscitation***							X
***Admission to nursery***							X
***Duration of hospital stay***							X
***Breastfeeding at discharge***							X
***Postnatal survey***						X	
***Economic analysis***							X

### Postnatal survey

Following birth all participating women will be asked to complete an electronic survey of their experiences of the injections and spray they received in the context of their labour and birth.

The survey is based on versions used in our previous studies and measures levels of satisfaction with pain relief, relaxation, likelihood to use in a subsequent labour and recommend to other women, most positive and negative aspects of the trial experience [15]. Survey data will be identifiable only through the allocated study participant code to enable matching with the allocated group in the clinical trial.

### Participant retention and completion of follow-up

As the primary and clinical outcomes data is collected prior to or at birth loss to follow-up is expected to be minimal. Therefore, there are no specific plans to promote participant retention beyond this timeframe. Reasons for discontinuing the injections or declining further rounds of injections (i.e. birth, progress to use of epidural, other maternal reason, other fetal reason (e.g. abnormal CTG)) will be collected by the midwife on the data collection form. For women who remain in hospital following their birth the survey will be completed on a tablet device. For those women opting for early discharge or discharged on weekends, a link to the survey will be emailed with one follow up contact from a research assistant within 2 weeks.

### Sample size

We have calculated the sample size based on the recommended minimal clinically significant reduction in VAS scores: 10 mm difference on a 100 mm VAS score between intervention and placebo [30]. To demonstrate a 10 mm reduction (SD 20 mm) in VAS scores with 80% power and 0.05 significance (two-sided) would require 64 participants per group. Based on previous studies [15] we estimate an attrition of 20% due primarily to women giving birth or requesting epidural analgesia prior to the measurement of the primary outcome. The total sample size required would be 154 participants, 77 per trial group.

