### Data analysis

All women who underwent randomisation and for whom primary outcome data is available will be analysed in their allocated treatment groups regardless of the intervention received (i.e. intention to treat). Randomisation should ensure that any baseline differences between groups occur by chance. To control for cluster effect repeated measurement, a linear mixed-model analysis will be conducted to investigate the difference in mean VAS score pre and post intervention. Missing VAS data will be addressed through imputation (last observation carried forward) A sensitivity analysis will be conducted following imputation to assess any effect on findings. Clinical data will be analysed on an available case basis with numbers of participants with missing data presented in the results tables. Categorical data will be analysed with chi-squared tests and non-repeated continuous variables will be analysed with t-tests if normally distributed or Mann-Whitney U test if non-normally distributed. Additional multivariable analysis will be employed if baseline differences are noted between the two groups. Treatment effects will be presented as mean difference or relative risks with 95% confidence intervals. All study outcomes will be analysed using a two-sided *P* value of < 0.05 to indicate statistical significance. We do not plan to undertake any subgroup analysis or interim analysis.

For the postnatal survey data descriptive statistics will be calculated for all variables, including mean, median, standard deviation, range, and percentages as appropriate. Free text responses will be analysed thematically.

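### The sample size adds 20% to 64 per group instead of allowing for a 20% loss, so 154 women fall slightly short of 80% power at the plan's own attrition rate

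*Protocol article*

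**What the plan says.** All the inputs stand in the Sample size section of the protocol article. The target is a "10 mm difference on a 100 mm VAS score between intervention and placebo". The next sentence gives the remaining design values and the evaluable number: "SD 20 mm) in VAS scores with 80% power and 0.05 significance (two-sided) would require 64 participants per group". The allowance for losses follows: "we estimate an attrition of 20% due primarily to women giving birth or requesting epidural analgesia prior to the measurement of the primary outcome". The section then concludes: "The total sample size required would be 154 participants, 77 per trial group". It does not say how the allowance was applied. The Methods part of the abstract repeats the total: "154 low-risk women in labour at term".

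The Data analysis section defines who is analysed: "All women who underwent randomisation and for whom primary outcome data is available will be analysed in their allocated treatment groups". It also plans a linear mixed model for the pre- and post-injection scores, and last observation carried forward for missing VAS scores with a sensitivity analysis.

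**The concern.** The section describes attrition as women who give birth or ask for an epidural before the 30-minute score is taken. Such losses come out of the women randomised, so the natural reading is that 20% of those randomised will have no primary outcome. The number to randomise is then the evaluable number divided by 0.80. The stated 77 per group looks like the evaluable number multiplied by 1.20, which allows for a smaller loss than the plan expects.

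At stake is whether the four stated figures (64 evaluable per group, 20% attrition, 154 randomised, 80% power) agree. If they do not, the article reports a power that its own total does not give under its own assumptions.

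**Working it through.** **Inputs** (all from the Sample size section): difference 10 mm; SD 20 mm; two-sided alpha 0.05; power 80%; 64 evaluable per group; attrition 20%; 77 per group, 154 in total.

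**Step 1: reproduce the 64.** The normal approximation is n = 2 × [SD × (z₀.₉₇₅ + z₀.₈₀) / difference]² = 2 × [20 × (1.960 + 0.842) / 10]² = 62.8 per group. The two-sample t-test, with standardised difference 10 / 20 = 0.5, gives 63.8, rounded up to 64. The stated 64 is right and matches the unadjusted t-test.

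**Step 2: reproduce the 77.** Adding 20% to the evaluable number gives 64 × 1.20 = 76.8, rounded up to 77 per group and 154 in total. This is exactly the stated figure.

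**Step 3: allow for a 20% loss of those randomised.** 64 / (1 − 0.20) = 80 per group, 160 in total. The difference is 160 − 154 = 6 women, or 6 / 160 = 3.75%. Starting from the normal approximation (63 after rounding up) does not give 77 either: 63 / 0.80 = 78.75, so 79 per group.

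**Step 4: what 154 leaves.** 77 × 0.80 = 61.6 per group, and 154 × 0.80 = 123.2 in total, against 2 × 64 = 128.

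**Step 5: power for 10 mm, SD 20 mm, two-sided 0.05.**

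| Evaluable per group | t-test power |
|---|---|
| 61 | 78.2% |
| 61.6 | 78.6% |
| 62 | 78.9% |
| 64 | 80.1% |

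The normal approximation at 61.6 per group gives 79.2%.

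**Step 6: the attrition that 154 can absorb.** 1 − 128 / 154 = 0.169. The stated total keeps 64 per group only if attrition is at most 16.9%, which is below the 20% assumed.

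**The case against.** Four points can be made for the plan.

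- **The denominator of the 20% is not stated.** This is true, but losses that occur before the outcome is measured are naturally a share of the women randomised. On that reading 77 is too few.
- **The planned analysis is not a plain t-test.** The Data analysis section plans a mixed model using pre- and post-injection VAS. If that model conditions on the pre-injection score, it may recover the loss. As an assumption, a baseline correlation of 0.1 to 0.5 gives about 79% to 89% power at 61.6 per group, and about 0.19 is enough for 80% by the t-test calculation. This point stands in part: a shortfall is not established for a baseline-adjusted analysis. But the article gives no correlation, entry at 60 mm or more may weaken it, and the Sample size section claims no such gain. It therefore does not correct the arithmetic.
- **Carrying the last observation forward may keep women in the analysis.** Table 1 schedules no labour-pain score between the pre-injection score and 30 minutes. For the primary outcome the value carried forward would be the pre-injection score, meaning no change. That adds no information on the effect and would tend to dilute a real difference. The Data analysis section also limits the analysis to women with primary outcome data.
- **The error is small beside the uncertainty in the inputs.** This stands. Attrition of 16.9% instead of 20%, or an SD of about 19.7 mm instead of 20 mm, would remove the shortfall.

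A reader might infer that the trial is seriously underpowered or has to enrol more women. The figures do not support that. The loss is about 1.4 percentage points, it depends on attrition reaching the full 20%, and it leaves bias, type I error and the analysis method untouched.

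**Conclusion.** The point holds as a minor arithmetic error. On the plan's own inputs, the total needed for 80% power at 20% attrition is 160, and the stated 154 comes from applying the allowance the wrong way round. The power statement of 78.6% (78.2% to 78.9% at 61 to 62 per group) rests on three conditions: attrition is counted among the women randomised, it reaches 20% in both groups, and the test is the unadjusted two-sample t-test that reproduces the 64. With attrition of 16.9% or less, the stated power is met.

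**What to change.** Correct the sample-size paragraph in one of two ways:

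- Keep 154 (77 per group) and state that it gives about 79% power at 20% attrition, and 80% if attrition is at most 16.9%.
- State 160 (80 per group) as the total required for 80% power at 20% attrition, and change the total in the abstract to match.

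The first is a wording change and needs no extra participants; its cost is a slightly less favourable stated power. The second means 6 more women if the larger total is recruited. If the sponsor wishes to claim a gain from baseline adjustment, it should be labelled as an assumption and given as a range of correlations, not as one figure.
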